**Methods:**

An estimated sixty patients will be enrolled in the study. Participants will be randomised to one of two conditions: CRT with treatment as usual (TAU), or TAU. CRT will consist of 42 individual sessions and 14 group sessions. The primary outcome measure for this study is change in cognitive functioning using the MATRICS Consensus Cognitive Battery (MCCB). Secondary outcomes include change in social and occupational functioning, disorganised symptoms, negative symptoms, violence, participation in psychosocial treatment and recovery. In addition to these effectiveness measures, we will examine patient satisfaction.

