### Cognitive remediation therapy

One approach that has shown potential to improve patients’ cognitive and motivational difficulties in non-forensic settings is cognitive remediation therapy [42–44]. Cognitive remediation therapy is a behaviourally based training approach designed to help patients improve their cognitive abilities and real world functioning. A variety of therapies exist under the cognitive remediation umbrella but most aim to either strengthen patients basic cognitive capacities through a process of drill and practice, or to teach patients more effective ways to deploy cognitive resources using meta-cognitive strategies. Cognitive remediation is a nonthreatening activity which patients enjoy and focuses on success and mastery experiences and therefore has the potential to increase self-efficacy [45]. A recent meta-analysis by Wykes has demonstrated that cognitive remediation is an effective intervention for patients with schizophrenia [42]. Within the Wykes meta-analysis, the average patient with schizophrenia or schizoaffective disorder who received cognitive remediation improved performance on cognitive tasks by an effect size of about .5 (Cohens d) and .42 on patient functioning. Also cognitive remediation therapy has been shown to produce durable improvements in cognition and functioning [42]. And there is evidence that cognitive remediation can optimise patients’ responses to psychosocial rehabilitation [46].

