### Participants

Approximately sixty patients under the care of the Central Mental Hospital will be recruited to participate in this study. Inclusion criteria are having a diagnosis of schizophrenia or schizoaffective disorder established using the Structured Clinical Interview for the Diagnostic and Statistical Manual IV (SCID) [55] and being proficient in English. Exclusion criteria are being acutely psychotic, being judged too dangerous to participate in treatment (positive symptoms combined with aggressive or self-harming behaviour in the last month) or being over 65 years of age. Inclusion criteria are broad and exclusion criteria are minimal because we are primarily interested in investigating whether CRT will be effective for a nationally representative cohort of forensic mental health patients.

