### Proposed analysis

Data analysis will be carried out using an intention to treat methodology [83]. Data from all enrolled participants will therefore be used in the analysis regardless of their level of participation in the study. Missing data will be estimated using multiple imputation [84]

The interaction between time i.e. baseline vs. 6 month and treatment condition (CRT vs TAU) on our primary outcome variable (MCCB composite cognition score) will be examined rather than between group differences, because tests of group difference average Time 1 (baseline) and Time 2 (6 month) assessments across the groups and consequently will be less sensitive to change. The interaction between time and treatment condition will be assessed using a repeated measure ANOVA with age and gender entered as covariates. This analysis will also be repeated at follow up using all three data points.

An a priori estimate of statistical power was completed using G*Power 3.1 [85]. Assuming a correlation greater than or equal to .5 between baseline and 6 month MCCB composite and a medium effect size (i.e. f = .25), the power to detect a statistically significant interaction between time and treatment conditions (i.e. CRT vs TAU) is adequately powered i.e. greater than or equal to .80. Should we find a statistically significant time X treatment condition interaction, post-hoc probing of the interaction will be completed with Bonferroni corrections applied where appropriate to maintain an alpha of 0.05.

SPSS PROCESS Macro Model 4 will be used to explore mechanisms of action should we find a positive impact of CRT. For example, whether change in cognition leads to a change in functioning, or whether a change in negative symptoms leads to a change in functioning etc. Change score will be calculated by subtracting the scores at baseline from the sores following the intervention. Age and gender will be entered as covariates in all mediation analysis. Bootstrapping will be used to estimate indirect effects, and 95 % bias-corrected confidence intervals using 1,000 bootstrap samples will be applied. A confidence interval that does not contain zero indicates statistically significant mediation (*p* < 0.05).

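### The stated power of at least .80 belongs to a 1.0 SD difference in change; for the 0.5 SD effect cited in the Background, 60 patients give about 48% at r = .5

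*Protocol article*

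**What the plan says.** The power statement is in the protocol article, Proposed analysis. The primary test is the time (baseline, 6 months) by treatment interaction on the MCCB composite, from a repeated-measures ANOVA with age and gender as covariates. Power was calculated in G*Power 3.1.

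- Correlation: "Assuming a correlation greater than or equal to .5 between baseline and 6 month MCCB composite".
- Effect: "a medium effect size (i.e. f = .25), the power to detect a statistically significant interaction".
- Conclusion: the interaction test "is adequately powered i.e. greater than or equal to .80".

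The power paragraph gives no sample size. The Participants section supplies it: "Approximately sixty patients under the care of the Central Mental Hospital". The paragraph also does not say what difference in MCCB change f = .25 stands for. The only anticipated effect on cognition anywhere in the document is in the Background section on cognitive remediation therapy, where a meta-analysis is summarised as showing that the average treated patient "improved performance on cognitive tasks by an effect size of about .5 (Cohens d").

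**The concern.** In a comparison of two independent groups at one time point, f = .25 and d = .5 are the same effect, and both are conventionally called medium. That equivalence does not carry over to the interaction in a two-group, two-occasion design, where the same f stands for twice the difference. The label therefore suggests an effect in line with the cited meta-analysis, while the calculation assumes one twice as large.

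This is the only power justification for the primary test. The Strengths section says the findings will inform whether CRT is rolled out in other jurisdictions. A reader who trusts the .80 could take a null result as evidence that CRT does not help forensic patients. At the bottom of the stated correlation range, such a result would occur about half the time even if the true benefit were 0.5 SD.

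**Working it through.** **Inputs.** From the article: N about 60 (Participants), two arms (abstract, Methods), two measurements in the primary test, f = .25, r of at least .5, and d of about .5 (Background). Assumed: 30 per arm, because no ratio is stated; two-sided alpha of .05 for the interaction test, because .05 is mentioned only for post-hoc probing; d expressed in raw-score SDs; no dropout.

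**1. Reproducing the stated figure.** G*Power's default within-between interaction uses λ = f² × N × m / (1 − r), with m = 2 measurements and, here, 1 and N − 2 degrees of freedom.

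- N = 60: λ = .0625 × 60 × 2 / .5 = 15; F(1, 58) gives power .968.
- N = 34: λ = .0625 × 34 × 2 / .5 = 8.5; F(1, 32) gives power .807.

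The statement of .80 or more is therefore true for f = .25 as entered. That 34 patients would already suffice is a first sign that the effect is large.

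**2. What f = .25 means here.** In a 2 × 2 design, a difference in change of δ puts an interaction effect of +δ/4 or −δ/4 in each of the four cells. The SD of these effects is δ/4, so f = δ / (4 SD), and f = .25 gives δ = 1.0 SD.

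Check through change scores, with 30 per arm and r = .5:

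- SD of change = SD × √(2(1 − r)) = SD × √1 = 1.0 SD.
- Standard error of the difference = SD × √(2/30) = 0.2582 SD.
- Noncentrality for δ = 1.0 SD: 1 / 0.2582 = 3.873, and 3.873² = 15, the same λ as in step 1. Power is again .968, and a simulation of 40,000 trials gave .969.

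**3. Power for 0.5 SD.** Here f = .5/4 = .125. At r = .5 the noncentrality is 0.5 / 0.2582 = 1.936, and power on 58 degrees of freedom is .478 (simulation .478).

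At other correlations the noncentrality is 0.5 / [√(2(1 − r)) × √(2/30)]:

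| r | Noncentrality | Power for 0.5 SD | Detectable at 80% power |
|---|---|---|---|
| .5 | 1.936 | .48 | 0.74 SD |
| .6 | 2.165 | .57 | 0.66 SD |
| .7 | 2.500 | .69 | 0.57 SD |
| .8 | 3.062 | .85 | 0.47 SD |

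Power crosses .80 at r of about .77. At r = .5, 80% power would take 128 patients. With an assumed 15% dropout (60 × .85 = 51 patients), power at r = .5 is .42.

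**4. The other G*Power options.** The option that defines f as in Cohen takes no correlation: λ = f² × N = .0625 × 60 = 3.75, power .478. The SPSS-style option gives λ = .0625 × 58 = 3.625, power .465. Neither reproduces .80 at N = 60. Because the article states a correlation as an input, the default option is the likelier one.

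**The case against.** The strongest reply is that the stated power is correct for its own inputs: f = .25 and r of at least .5 give .97 with 60 patients. That stands. The fault lies in what this f represents and in calling it medium.

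Second, the power paragraph never mentions d = .5, so treating it as the design effect is an inference from the Background. This also stands as a matter of labelling. The inference is still the natural one: no other effect on cognition is given, it matches the word medium, and nothing in the article supports expecting 1.0 SD.

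Third, 48% is the value at the floor of the stated range, and the article describes the MATRICS battery as highly reliable, so the true correlation may be higher. That is fair, and the range should be shown. But the article claims adequacy for every r from .5 upward, and for 0.5 SD the claim fails from .5 to about .77.

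Fourth, the article does not say how the meta-analytic d was standardised. If it were in SDs of change rather than raw scores, power would be .48 at every r, so this uncertainty does not help the claim.

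Finally, a single national service with 94 secure beds and 13 community beds may have little room to enlarge the sample. That is a reason not to ask for more patients. It does not justify leaving the statement as it is.

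**Conclusion.** The concern holds. The claim of at least .80 is right only for a 1.0 SD between-group difference in change. For the 0.5 SD effect that the article itself cites, power with 60 patients is about 48% at r = .5 and passes 80% only from r of about .77. No G*Power option gives .80 for 0.5 SD throughout the stated range of r. The figures rest on equal allocation, two-sided alpha of .05, a raw-score SD scale for d and complete follow-up; dropout would lower them. The statement must be corrected because it is the sole support for the primary test's ability to detect the expected benefit.

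**What to change.** Rewrite the power paragraph in SD units of the MCCB composite, giving the sample size, allocation ratio, alpha and G*Power option. Possible wording:

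*With 60 patients (30 per arm, two-sided 5%, no dropout), the time by group test has 48% power at r = .5 and 85% power at r = .8 for a 0.5 SD difference in change. The difference detectable with 80% power is 0.74 SD at r = .5 and 0.47 SD at r = .8.*

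Remove the description of the trial as adequately powered for all r of .5 or more, and the description of f = .25 as a medium effect for this test. Add a line on expected dropout.

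Optionally, if the team chose to adjust for baseline by ANCOVA instead of testing the interaction, the figures to quote for 0.5 SD would be those of that model. With residual SD = SD × √(1 − r²) and 57 degrees of freedom, they are 59% at r = .5, 76% at r = .7 and 89% at r = .8. That would be a change of model and is not needed to correct the statement.

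The cost is one paragraph of wording and a less favourable number. Sample size, endpoint, primary test and trial conduct stay as they are.

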### Primary outcome measure: change in global cognitive functioning

Cognitive functioning among study participants will be assessed at baseline, end of treatment (approximately 6 months) and 8 month follow up using the MATRICS Consensus Cognitive Battery (MCCB) global composite score [61]. The MATRICS battery covers seven cognitive domains: processing speed; attention/ vigilance; working memory; verbal learning; visual learning; reasoning and problem solving; social cognition assessed using social reasoning tasks for understanding and managing emotions taken from the Managing emotions subtest of the Mayer-Salovey-Caruso Emotional Intelligence Test (MSCEIT) which is a social reasoning test. The test comprises of vignettes of various situations, and options for coping with the emotions depicted in these vignettes [80, 81]. Participants are required to indicate the effectiveness of each solution ranging from one (very ineffective) to five (very effective). In validation studies, and in antipsychotic trials of stable patients, the MATRICS demonstrated excellent reliability, minimal practice effects and significant correlations with measures of functional capacity. It is hypothesised that there will be a group by time interaction (CRT vs TAU) on the total score of the MATRICS battery at the end of treatment approximately 6 months and at 8 months follow up.

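### When CRT moves the mediator, the planned change-score mediation rule can declare mediation from a shared cause alone

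*Protocol article*

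**What the plan says.** The Proposed analysis section of the protocol article fixes the mediation analysis in some detail.

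- Model and trigger: "SPSS PROCESS Macro Model 4 will be used to explore mechanisms of action should we find a positive impact of CRT".
- Question, given by example: "whether change in cognition leads to a change in functioning, or whether a change in negative symptoms leads to a change in functioning".
- Variables: "Change score will be calculated by subtracting the scores at baseline from the sores following the intervention". One rule serves mediator and outcome, and no visit or lag is named.
- Covariates: "Age and gender will be entered as covariates in all mediation analysis".
- Interval: "95 % bias-corrected confidence intervals using 1,000 bootstrap samples will be applied".
- Decision rule: "A confidence interval that does not contain zero indicates statistically significant mediation".

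Other sections bear on this. The MCCB is "assessed at baseline, end of treatment (approximately 6 months) and 8 month follow up". SOFAS and the symptom scales carry hypotheses at the end of treatment and at eight months. The HCR-20, DUNDRUM-3 and DUNDRUM-4 are measured only at baseline and eight months. Under Treatment as usual, antipsychotic dose and anticholinergic load are recorded at every assessment, and medication may change. The Limitations section concedes that medication cannot be held constant. It does not mention time order or mediator-outcome confounding.

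**The concern.** Randomisation protects the path from CRT to the mediator and the path from CRT to the outcome. It does not protect the path from mediator to outcome, which is an observational regression within arms. If both changes run over the same window, that regression cannot tell cognition driving functioning from functioning driving cognition, or from a third factor acting on both. A medication change is one such factor that the article itself identifies. It is measured but left out of the model, as are the baseline levels of mediator and outcome.

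The decision rule then turns a non-zero indirect effect into a significant finding on the question "whether change in cognition leads to a change in functioning". That cognition underlies functioning is a central part of the rationale in the Background and Discussion, so a positive mediation result would be read as confirming it.

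**Working it through.** **Inputs.** From the article: about 60 patients (Participants); effects of about 0.5 on cognition and 0.42 on functioning (Background, Cognitive remediation therapy); f = .25 and correlation .5 (power statement); age and gender as covariates; 1,000 bias-corrected resamples. Assumed: 30 per arm, normal change scores with SD 1, no missing data, and a within-arm correlation r between the two changes of 0 to .5.

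**The plan's own figure.** The only stated power (at least .80) concerns the primary interaction. With the G*Power default, lambda = N·f²·m/(1−rho) = 60 × 0.0625 × 2/0.5 = 15 on 1 and 58 df, and power is 0.968. The statement reproduces. The same inputs imply a between-arm difference in change of 4f = 1.0 SD, because the SD of change is √(2(1−.5)) = 1 score SD. This gives a second, larger effect to test. No figure is stated for the mediation analysis.

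**What the model estimates.** Let a be the CRT effect on mediator change and b the within-arm slope of outcome change on mediator change. The indirect effect is a × b. With unit SDs and no causal path from mediator to outcome, b equals r. The spurious indirect effect is then a × r:

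- r = .2: 0.5 × .2 = 0.10, which is 0.10/0.42 = 24% of the total effect
- r = .3: 0.5 × .3 = 0.15, or 36%
- r = .5: 0.5 × .5 = 0.25, or 60%

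**Simulation of the stated rule.** 1,000 trials per row, true mediator-to-outcome effect zero throughout (Monte Carlo standard error at most 1.6 points for all trials). The last column keeps only trials with a significant positive CRT effect on the mediator. This is one way to operationalise the plan's condition of a positive impact.

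| CRT effect on mediator | CRT effect on outcome | r | Mediation declared, all trials | Among trials passing the condition |
|---|---|---|---|---|
| 0 | 0 | .3 | 6% | about 2% pass; too few |
| 0 | 0 or 0.5 | .5 | 7-8% | about 2-3% pass; too few |
| 0.5 | 0.42 | 0 | 5% | 10% |
| 1.0 | 0.42 | 0 | 7% | 7% |
| 0.5 | 0.42 | .2 | 23% | 41% |
| 0.5 | 0.42 | .3 | 37% | 72% |
| 0.5 | 0.42 | .5 | 56% | 99% |
| 1.0 | 0.42 | .3 | 68% | 69% |
| 1.0 | 0.42 | .5 | 96% | 98.5% |

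Two ingredients are needed for a large error: a CRT effect on the mediator and correlated individual changes. When both are present, the plan's condition raises the rate at the smaller effect.

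**Interval type.** With no shared cause and a 0.8-1.0 SD effect on the mediator, bias-corrected intervals excluded zero in 7.7-8.4% of trials and percentile intervals in 4.4-5.3%.

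**Would a lag help?** Several simulations assumed a state shared by mediator and outcome at each visit, a 0.7 SD effect on the mediator and no true path. The same-visit rule gave between 19% and 93% false mediation, depending on the assumed strength and persistence of the state. Adjusting the same-visit model for baseline values alone did not help. Results for a 6-month mediator with an 8-month outcome were:

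- Adjusted for baseline values only: the rate fell in many scenarios (10-47%), but was 63% under one set of inputs with persistence .5 and 84-88% when the shared cause was highly or fully persistent.
- Adjusted also for the 6-month outcome: mostly 4-13%, but 21% at persistence .8 and 45% for a fully persistent cause.
- Power: for a true effect already present at 6 months, adding the 6-month outcome cut power from about 77-85% to 1-8%. Another set of inputs, with a true path of .5, gave 19-27%.

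**The case against.** The strongest reply is that this analysis is exploratory, conditional and illustrative. The stated aims are efficacy and satisfaction, and mediation is not among them. The wording about one change leading to another frames a question. An article may also leave visit windows and sensitivity analyses to a fuller plan. This stands in part: the CRT-versus-TAU comparisons do not depend on the model. It does not remove the point, because the article itself states the covariates, the change-score formula, the interval and the significance rule.

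Three stronger readings are tempting, and the documents do not support them.

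- A reader might infer that mediation will be declared whenever the two measures move together, or whenever CRT improves cognition at all. The first needs a CRT effect on the mediator as well. The second needs correlated individual changes. Without either ingredient the rate stays at about 5-8% overall (7-10% among trials passing the condition when r is zero).
- A reader might infer that the plan states same-visit changes. It does not name the visit. Same-visit change is the natural reading, chiefly for SOFAS and symptoms. For the HCR-20 and DUNDRUM scales only an 8-month change exists, so a mediator taken at 6 months would already precede the outcome.
- A reader might infer that lagging the outcome cures the problem. The simulations above show that it does so only in part.

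**Conclusion.** The point holds in a limited form. As written, the rule sets no time order, omits plausible mediator-outcome confounders that the trial will measure, and treats a non-zero indirect effect as significant mediation. When CRT moves the mediator and a shared cause correlates the changes within arms, false mediation far exceeds the nominal 5%: 23-56% for r of .2-.5 at the effect sizes the article cites, and 41-99% among trials with a significant effect on the mediator.

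The size depends on r, which the documents do not give, and on treating the cited effects as SDs of change. Missing confounder adjustment and the causal reading remain a problem even if the two changes come from different visits. Bias-corrected intervals add a smaller, secondary error. The primary result is not affected. The change is worth making because it is cheap, not because the trial's main conclusion is at risk.

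**What to change.** 1. Replace bias-corrected with percentile bootstrap intervals.
2. Name the visit for each mediator and outcome. Where both visits exist, add a time-ordered analysis with the mediator at 6 months and the outcome at 8 months. Adjust it for baseline mediator, baseline outcome, age, gender and the medication measures already collected. Report it with and without the 6-month outcome.
3. Drop the rule that an interval excluding zero shows that one change leads to the other. Report the indirect effect with its interval as associational and dependent on no unmeasured mediator-outcome confounding.

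**Cost.** No new data are needed, only analysis text and a few extra models. The lagged model has less power, markedly so with the 6-month outcome included, and then answers a narrower question: change after 6 months. Patients without an 8-month visit contribute less. Adjustment for the 6-month outcome is impossible for the HCR-20, DUNDRUM-3 and DUNDRUM-4. Confounding by a persistent cause remains in every version, so the associational wording in item 3 is needed whichever model is used.

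### With 1,000 bootstrap samples and a zero-crossing rule, another random seed would reverse the exploratory mediation verdict in roughly 2.5-5.6% of trials under moderate assumed paths; 10,000 samples would cut this to about 1-2%

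*Protocol article*

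**What the plan says.** All of the following is in the protocol article, Proposed analysis, unless stated otherwise.

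- The tool is "SPSS PROCESS Macro Model 4". It "will be used to explore mechanisms of action should we find a positive impact of CRT", so the analysis is exploratory and conditional. The examples given are change in cognition, or change in negative symptoms, leading to change in functioning.
- "Age and gender will be entered as covariates in all mediation analysis".
- Indirect effects are bootstrapped at the 95% level: "bias-corrected confidence intervals using 1,000 bootstrap samples will be applied".
- The decision rule is binary: "A confidence interval that does not contain zero indicates statistically significant mediation", with p < 0.05 attached.
- On sample size, the abstract (Methods) says: "An estimated sixty patients will be enrolled in the study". The allocation ratio is not stated.

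The article gives no figure for simulation error in these intervals and no assumed size for the mediator-to-outcome path.

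**The concern.** A bootstrap limit is itself an estimate and varies from run to run. When the whole verdict turns on which side of zero the limit falls, that variation can decide it. Bias correction adds to the noise, because its constant is estimated from the same draws and enters the limit with a factor of two.

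What is at stake is whether the mechanism statement can be reproduced: on identical data, mediation could be declared or not depending on the seed. This is separate from whether a bias-corrected interval holds its nominal error rate, and from whether a mediation model supports a causal reading.

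**Working it through.** **Plan's own figure.** The section states no bootstrap-error figure to reproduce. Its only quantitative claim nearby is power of at least 0.80 for the primary interaction. With f = 0.25, correlation 0.5, two time points and N = 60, the noncentrality is 0.25² × 60 × 2 / (1 − 0.5) = 15, and F on 1 and 58 df gives power 0.968. The claim reproduces but does not bear on mediation.

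**Step 1: error of the limit at B = 1,000.**
- Tail proportion: SE = √(0.025 × 0.975 / 1000) = 0.0049. The 95% Monte Carlo range of a nominal 2.5% tail is 0.025 ± 1.96 × 0.0049, about 1.5% to 3.5%, or a two-sided p of about 0.031 to 0.069.
- Bias-correction constant: SE = √(0.25 / 1000) / 0.399 = 0.040 on the z scale.
- Combined, on the z scale, with normal density 0.0584 at the 2.5% point: variance = (0.00494/0.0584)² + 4 × 0.0396² − 4 × (0.025 × 0.5 / 1000) / (0.0584 × 0.399) = 0.0071 + 0.0063 − 0.0021 = 0.0113, so SD ≈ 0.106.

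**Step 2: chance that two runs disagree, at about 50% power for mediation.** Approximation: 2 × SD × 0.399 × 0.564.
- B = 1,000: 2 × 0.106 × 0.399 × 0.564 ≈ 4.8%.
- B = 10,000: the SD shrinks by √10 to about 0.034, giving ≈ 1.5%.

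**Step 3: simulation.** Inputs: N = 60, 30 per arm (assumed), normal errors (assumed). Path a is the standardised effect of CRT on the mediator; the Background section on cognitive remediation therapy cites about 0.5 for cognition. Path b, mediator to outcome, is not in the document and is varied. Set A has 1,500 trials per setting and no direct effect. Set B has 300-400 trials per setting, a direct effect of 0.2, and age and gender as covariates.

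Chance that two runs on the same data give opposite verdicts:

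| a, b | Set A, B = 1,000 | Set B, B = 1,000 | Set B, path a significant | Set A, B = 10,000 |
|---|---|---|---|---|
| 0.5, 0.3 | 4.6% | 5.6% | 4.1% | 1.3% |
| 0.5, 0.5 | 4.9% | 5.5% | 2.0% | 1.8% |
| 0.8, 0.3 | 4.7% | 4.9% | 4.3% | 1.5% |
| 0.8, 0.5 | 2.5% | 2.8% | 1.1% | 0.7% |
| 0.5, 0.39 | – | 5.2% | 3.0% | – |
| 0.67, 0.39 | – | 4.3% | 2.4% | – |
| 0.5, 0.14 | – | 3.0% | 3.5% | – |
| 0.5, 0 | – | 0.8% | 1.1% | – |
| 0, 0 | – | 0.1% | too few trials (19) | – |

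A further check at a = 0.5, b = 0.3 (200 trials) gave 4.7% at 1,000 samples and 2.0% at 10,000. In Set B at a = 0.5, b = 0.39, 5,000 samples gave 2.4% (120 trials).

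The approximation and the simulations agree: about 5% near 50% power, less as mediation becomes either clear or absent, and roughly a threefold reduction at 10,000 samples.

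**The case against.** **Scope.** The analysis is exploratory and gated on a positive impact of CRT, and a reversal needs a limit close to zero. This stands and keeps the point minor. The gate does not remove it: with path a of at least 0.5 and significant, 1.1-4.3% of re-runs still disagree. That conditioning is also only a proxy. A positive impact on cognition does not imply a significant path to negative symptoms, the other mediator named.

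**Unsupported inputs.** The rate depends on a mediator-to-outcome path that the article does not give. This also stands, so the rate is given as a range over stated assumptions.

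**Missing detail.** A seed is programming detail that may sit in an unseen analysis plan, and its absence here is no fault. The article also already plans to estimate the indirect effect with an interval. Both objections stand. What remains is the resample count, which the article itself fixes at a low value.

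**A tempting stronger reading.** A reader might infer that about one trial in seven has a seed-dependent verdict. Such figures (8-19% in the settings with b of 0.3 or more) count trials in which 20 separate runs are not unanimous. The plan describes no such set of runs, the count grows with the number of seeds tried, and it falls to 0.5-3.0% when b is zero. The document therefore does not support one in seven as a property of the plan. Nor does it give grounds to suggest that anyone would re-run until an interval excludes zero.

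**Limits of the check.** Multiple imputation, which the plan uses for missing data, was not simulated. It has random draws of its own, so a bootstrap seed alone would not make the whole analysis reproducible.

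**Conclusion.** The point holds at minor severity. One thousand samples is low for a bias-corrected limit judged solely by whether it crosses zero. At N = 60, with path a of 0.5-0.8 and path b of 0.3-0.5, a single re-run would reverse the verdict in roughly 2.5-5.6% of trials. This rests on equal allocation, normal errors and complete data, and on a path b that is assumed throughout.

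The primary and secondary group-by-time tests do not use this bootstrap, so a reader should not carry the concern over to them.

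**What to change.** In Proposed analysis, replace the 1,000 bootstrap samples by at least 10,000. This applies whichever type of bootstrap interval is kept. Record the seed with the analysis program so that the reported interval can be regenerated.

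The cost is one number in the text, one recorded value and seconds of computing time. Design, data collection and sample size do not change.

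### The mediation rule is labelled p < 0.05, but for the lead cognition-to-functioning pathway it declares mediation falsely in about 9% of trials of about 60 patients

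*Protocol article*

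**What the plan says.** All of this is in the Proposed analysis section of the protocol article unless noted.

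- Model and trigger: "SPSS PROCESS Macro Model 4 will be used to explore mechanisms of action should we find a positive impact of CRT".
- First example pathway: "whether change in cognition leads to a change in functioning". The second is change in negative symptoms leading to change in functioning, and the list is left open. Mediators and outcomes are change scores.
- Covariates: "Age and gender will be entered as covariates in all mediation analysis".
- Interval: 95% "bias-corrected confidence intervals using 1,000 bootstrap samples will be applied".
- Decision rule: "A confidence interval that does not contain zero indicates statistically significant mediation", followed in brackets by p < 0.05.
- Size (Participants section): "Approximately sixty patients under the care of the Central Mental Hospital will be recruited to participate in this study".

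The Bonferroni sentence in the same section concerns post-hoc probing of the time by treatment interaction. It does not touch the mediation rule.

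**The concern.** The protocol fixes the interval and the decision rule, and it states an error level for that rule. The statement can therefore be checked.

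The indirect effect is the product of two paths, CRT to mediator (a) and mediator to outcome (b). It is zero when either path is zero. In small samples the bias correction shifts the percentile limits by an amount that is itself estimated with noise. When one path is clearly non-zero and the other is zero, the interval then excludes zero too often.

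The lead example falls into that situation. Cognition (the MCCB composite) is the primary outcome, and the mediation analysis is run only after CRT is found to work. A significant effect on cognition means that path a is already significant, so the test rests almost wholly on path b.

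At stake is a statement that gains in cognition produce the gains in functioning, reported at a 5% error level that the method does not deliver.

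**Working it through.** **1. The plan's own power figure.** For the interaction in a two-group, two-time design, the noncentrality is λ = N·f²·m/(1 − ρ) with df 1 and N − 2. With N = 60, f = 0.25, m = 2 and ρ = 0.5, λ = 60 × 0.0625 × 2/0.5 = 15 and power is 0.968. At N = 34, λ = 8.5 and power is 0.807. The stated power of at least 0.80 is correct.

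**2. Effect sizes for path a.** A two-group comparison of change scores has λ = N·d²/4. Setting this to 15 gives d² = 1, so the design effect is 1.0 SD of change. The Background section (Cognitive remediation therapy) cites about 0.5 for cognition. The range 0.5 to 1.0 SD thus has support in the document.

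**3. The rule.** Fit M on arm, age and gender, and Y on arm, M, age and gender; the estimate is a·b. Draw 1,000 case resamples. Let z₀ = Φ⁻¹(share of bootstrap values below the estimate). The bias-corrected limits are the Φ(2z₀ ± 1.96) quantiles of the bootstrap values. The percentile limits are the 2.5% and 97.5% quantiles.

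**4. Lead pathway, b = 0.** Assumed: 30 per arm (the allocation ratio is not stated), normal errors, complete data. 12,800 trials were simulated per setting, and those with a significant positive CRT effect on the mediator were kept.

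| CRT effect on mediator (SD) | Direct effect | Trials kept | Bias-corrected | Percentile | t test of b |
|---|---|---|---|---|---|
| 0.5 | 0 | 5,925 | 9.8% | 5.0% | 5.1% |
| 0.5 | 0.5 | 5,860 | 9.2% | 5.2% | 5.5% |
| 0.71 | 0 | 9,681 | 9.3% | 5.5% | 5.0% |
| 1.0 | 0 | 12,339 | 8.7% | 5.9% | 4.8% |
| 1.0 | 0.5 | 12,353 | 8.7% | 5.7% | 4.9% |
| 1.5 | 0 | 12,796 | 7.8% | 6.3% | 5.0% |

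Monte Carlo standard errors for the bias-corrected column are about 0.2 to 0.4 points; for example √(0.0977 × 0.9023/5,925) = 0.004. Repeat runs of 3,000 kept trials gave 8.9% and 10.2% at 0.5 SD, and 8.6% and 8.7% at 1.0 SD. A further run at 0.5 SD gave 9.6% with 50 or 40 evaluable patients, against 5.1% and 5.0% for the percentile interval.

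Within each row only the method of inference differs, so the excess comes from the bias correction.

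**5. Lead pathway without selecting on path a.** For effects of 0.5, 0.71, 1.0 and 1.5 SD the bias-corrected rates are 5.2%, 7.4%, 8.5% and 7.8%.

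**6. Negative symptoms as mediator.** Here the trigger was a significant effect on cognition. Assumed: a CRT effect of 0.7 SD on cognition and a correlation of 0.3 between the two changes. Bias-corrected rates with 60 patients:

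| Path a (SD) | Path b | Rate |
|---|---|---|
| 0 | 0 | 0.7% |
| 0.2 | 0 | 1.6% |
| 0.3 | 0 | 2.5% |
| 0.5 | 0 | 6.7% |
| 0 | 0.3 | 5.3% |
| 0 | 0.5 | 8.2% |

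If the trigger is instead a true CRT effect on the outcome, with a = 0 and b = 0.59, the rate is 7.0% to 9.3%. Settings in which the trigger is itself a chance finding are left out.

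**7. Power for a real indirect effect** (n = 60, b = 0.3, significant effect on the mediator). At a = 0.5 power falls from 65.5% (bias-corrected) to 53.3% (percentile), 12.2 points. At a = 0.8 it falls from 66.1% to 56.6%, 9.5 points. A repeat gave 66% to 53% and 67% to 58%, or 13 and 9 points.

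**The case against.** The strongest case is that this is a contingent exploration. Mediation is not among the aims in the Hypotheses section or the outcomes in Table 2, and the protocol's word is explore. In a cohort of about sixty, some excess of false positives may be a fair price for sensitivity, since the alternative costs more points of power than it saves in error. The percentile interval is not exact either: it gives about 6% at 1.0 SD.

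These points limit the importance of the finding and show that the change has a price. They do not make the stated error level correct. A plan may accept a liberal rule, but it should not then label it p < 0.05.

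A reader might also infer that the error rate is nearly doubled for every pathway. The document does not support that. Its trigger is "will be used to explore mechanisms of action should we find a positive impact of CRT", which does not require a significant effect on each mediator. A positive result on cognition does not select the path from CRT to negative symptoms, and there the rate can be far below 5%.

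Nor should 1,000 resamples be blamed. The percentile interval from the same 1,000 resamples is close to nominal, and no calculation here attributes any of the excess to their number.

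**Conclusion.** The concern holds for the lead pathway. With about 60 patients, a significant CRT effect on cognition and no effect of cognition on functioning, the rule declares mediation in about 9% of trials (8.6% to about 10% for CRT effects of 0.5 to 1.0 SD) against a stated 5%. For other pathways the rate runs from under 1% to about 8-9% according to which path is null, so the label cannot be relied on there, but no single inflation figure applies.

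The figures rest on assumed path sizes, 1:1 allocation, normal errors and complete data. The multiple imputation that the plan specifies was not simulated.

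It would go too far to read this as a threat to the trial's main conclusion. It concerns an overstated significance label on an exploratory mechanism claim, and the primary analysis and its power statement are unaffected. The correction is still worth making, because it needs only a change of wording.

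**What to change.** Either of two changes is enough.

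1. Keep PROCESS Model 4, the covariates and the change scores, but replace the bias-corrected interval with the 95% percentile bootstrap interval. On the same data this brings the lead-pathway rate to about 5% to 6%.
2. Keep the bias-corrected interval, remove the p < 0.05 equivalence, and report the interval as exploratory without a significance claim.

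More resamples would be harmless but are optional and are not the cure.

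The first option costs one change of wording and about 9 to 13 points of apparent power for the indirect effect in the settings above. Part of that loss is the bias-corrected interval's excess of false positives. The second option costs no power but gives up the formal claim of significance.
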